### Treatment integrity

A random selection of 20% of sessions will be audio-taped and rated for compliance with the treatment manual by an independent clinician (PhD level Clinical Psychologist) blind to treatment condition. The Cognitive Therapy Scale [98] will be employed to assess therapist competence.

### Follow-up

At the end of treatment and at three and six months after treatment completion, participants will be reassessed by an experienced independent research assistant blind to treatment condition. Participants will be reassessed on the main outcome measures in addition to the Drinker Inventory of Consequences (DRINC) [89], Kushner’s Alcohol Outcome Expectancies Questionnaire [74], the OTI, the Penn Craving Scale [77], Alcohol Expectancies Social Anxiety (AESES) [91], University of Rhode Island Change Assessment (URICA) [79], and the Health Service Utilisation questions [80].

### Analyses

Random effects regression models will be used to compare the efficacy of the treatment conditions on outcome measures from an intention to treat perspective. Random effect regression models (also known as hierarchical linear or mixed models) have been used in clinical trials involving relapse, and are suited to repeated measures, missing observations, and longitudinal data [99]. Random effects regressions can also account for variance associated with the clustering found with group treatment and multiple treatment sites. Cox regression will be used to determine time from baseline to first drink, time to first heavy drink. Last-point carried forward or multiple imputation will be used to determine the scores of participants who drop-out and are not located at follow-up.

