### Procedure

After baseline assessment, all participants will complete a pre-treatment session of motivational interviewing followed by a 1 month “washout” period of abstinence. Symptoms of social anxiety (SPS and SIAS), general anxiety and depression (DASS) will then be reassessed. After reading and signing a written information and consent form, participants will be individually randomised by the sealed envelope method to one of two treatment conditions, of either: i) Treatment for alcohol use disorder comprising 9 weekly sessions of individual CBT for alcohol use disorder; OR ii) Treatment for alcohol use disorder and social anxiety disorder comprising 9 weekly sessions of integrated individual CBT for alcohol use disorder and anxiety disorder.

Each therapy session will last 60 to 90 minutes and will be conducted by one therapist (Clinical Psychologist). Both treatment conditions will have the same therapists and equal exposure to face-to-face treatment, approximately 10–15 hours, over a total of approximately three to five months.

Participants will be encouraged to attend treatment sessions weekly where possible, but will be given a maximum time frame of 5 months from initial assessment in which to complete treatment. Post and follow up assessment time points will be calculated from the end of all treatment sessions (1 motivational interviewing session plus 9 treatment sessions).

Participants will be considered non-completers if they miss more than 2 treatment sessions, or if they fail to complete the course of treatment within five months from assessment. Therapists will make at least 3 attempts to reschedule missed appointments, followed by a handwritten note two weeks after the last phone contact to i) acknowledge client’s decision to leave treatment, ii) encourage return to treatment, and iii) provide information about how this can be achieved. Participants who nevertheless choose to discontinue treatment will be contacted for post and follow up assessments calculated as if treatment were completed 3 months from the initial assessment.

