### Treatment and treatment sites

Treatment will be provided at the Emotional Health Clinic, Centre for Emotional Health, Macquarie University, or Drug Health Services at Royal Prince Alfred Hospital (Sydney South West Area Health Service) and comprise one pre-treatment session followed by 9 weekly sessions. Two additional supplementary sessions can be used at treating therapist discretion to deal with crises that may emerge. The therapeutic approach will integrate CBT skills with a motivational interviewing style. Participants will complete monitoring diaries daily (recording the number of drinks consumed and rating their mood, anxiety and craving for alcohol), read educational material and complete take home tasks. The treatment goal is short-term abstinence (≥3 months), with participants selecting individual goals within recommended drinking guidelines beyond that period.

After an initial “washout” period of abstinence (≥ 1 month), goals for alcohol reduction will be determined collaboratively. Thus, participants may select a goal of abstinence, or controlled use within recommended drinking guidelines. Offering a choice of treatment goals will facilitate the inclusion of participants with various levels of dependence and decrease the risk of early drop-out [93].

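### The secondary Cox endpoints run from baseline, which precedes the washout and, on the natural reading, randomisation, so drinking before allocation counts as an event and dilutes the hazard ratio

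*Protocol article*

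**What the plan says.** The Analyses section of the protocol article sets the time origin: "Cox regression will be used to determine time from baseline to first drink, time to first heavy drink". The origin is attached to the first drink and only implied for first heavy drinking. Both are listed under Secondary outcome measures, where relapse is defined by three consecutive heavy-drinking days.

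The Procedure section gives the sequence. It opens: "After baseline assessment, all participants will complete a pre-treatment session of motivational interviewing followed by a 1 month" washout. Symptoms are measured again after the washout ("general anxiety and depression (DASS) will then be reassessed"), and the next sentence reads: "After reading and signing a written information and consent form, participants will be individually randomised by the sealed envelope method". Treatment and treatment sites confirms the minimum length of the washout: "period of abstinence (≥ 1 month), goals for alcohol reduction will be determined collaboratively".

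On visit dates, Procedure says: "Post and follow up assessment time points will be calculated from the end of all treatment sessions". Treatment may take up to 5 months from initial assessment. Those who discontinue have "assessments calculated as if treatment were completed 3 months from the initial assessment".

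**The concern.** A randomised comparison of time to event should start when the arms begin to differ, which is at allocation. Here the clock starts at least about a month earlier. Baseline does not require abstinence: the Assessment section asks only for three days at low-risk levels. No rule excludes or sets aside people who drink during the washout. Anyone who does so has already had the first-drink event when the envelope is opened, and nothing they do after treatment starts can contribute to that endpoint.

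Hypothesis 2 says the integrated arm will hold its lower consumption for longer, and these endpoints bear directly on that. The risk is a comparison weakened by events that carry no information about treatment.

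A smaller related matter is that the same nominal visit can fall at different times since randomisation, depending on whether the participant completed therapy.

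**Working it through.** **Which assessment is baseline?** Three pieces of text bear on this.
- Procedure puts the washout after the baseline assessment.
- The paragraph on blood tests under Table 1 uses the same word for samples that the table schedules at pre-treatment and not at post-washout.
- Table 1 has no column called baseline. It has separate pre-treatment and post-washout columns, with the TLFB in both.

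The first two agree, so the word most naturally means the assessment before the washout. The gap to randomisation is then at least 1 month.

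**Size of the dilution.** The protocol states no hazard ratio, event count or power for the Cox analyses, so there is no figure to reproduce. Assumed inputs, none from the protocol except N:
- N = 200 (the planned total), 1:1, two-sided 5%
- true post-randomisation hazard ratio 0.65
- control median 60 days to first drink, exponential times
- 240 days of follow-up after randomisation, 30-day washout
- a share q with a first drink in the washout, equal in the two arms

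Probability of an event within 240 days of randomisation:
- control: 1 − 2^(−240/60) = 0.9375
- integrated: 1 − 2^(−0.65 × 240/60) = 0.835
- mean p = 0.886

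On the baseline clock:
- total events D = 200 × [q + (1 − q)p]
- share of events after allocation s = (1 − q)p / [q + (1 − q)p]
- pre-allocation events have a log hazard ratio of zero, so approximately log HR = s × ln 0.65 = −0.431s
- z = |log HR| × √(D/4), and power = Φ(z − 1.96)

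For q = 0.50: s = 0.443/0.943 = 0.470, HR = exp(−0.431 × 0.470) = 0.817, D = 188.6, z = 0.202 × √47.15 = 1.39, power = Φ(−0.57) = 0.28.

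| q | D | s | HR | Power |
|---|---|---|---|---|
| 0 (same as randomisation clock) | 177.3 | 1.00 | 0.65 | 82% |
| 10% | 179.5 | 0.89 | 0.68 | 73% |
| 25% | 182.9 | 0.73 | 0.73 | 56% |
| 50% | 188.6 | 0.47 | 0.82 | 28% |
| 75% | 194.3 | 0.23 | 0.91 | 10% |

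Simulated trials with fitted Cox models agree: hazard ratios of 0.64–0.65 with no washout drinking, then 0.67–0.68, 0.72–0.73, 0.81–0.82 and 0.90–0.91. Power is 81–82%, then 72–73%, 54–58%, 27–28% and 10–11%. A separate set-up (true HR 0.60, half of controls with an event by 6 months) shows the same pattern, from 0.65 at q = 10% to 0.91 at q = 70%.

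**Visit dates.** The earliest completion is a 1-month washout plus 9 weekly sessions: 1 + 9/4.35 = 3.07 months from assessment. The latest is 5 months.

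| Visit | Discontinued (months from assessment) | Completed |
|---|---|---|
| Post | 3 | 3.1–5 |
| 3-month | 6 | 6.1–8 |
| 6-month | 9 | 9.1–11 |

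The gap between two people is therefore about 0 to 2 months. The gap between arm means is roughly the difference in attrition times the lag. With an assumed 10-point difference and 1-month lag it is 0.10 × 30.4 = 3 days. With 20 points and the full 2 months it is 0.20 × 60.9 = 12 days.

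**The case against.** The Analyses section does not define baseline, and a first drink makes most sense after an abstinent month, so the post-washout TLFB could be the intended origin. The place of randomisation rests on sentence order, in a paragraph that also mentions signing the consent form only after the baseline assessment and washout and so may not be strictly chronological. The flowchart that might settle this is not available. This stands as a limit on certainty: the sequence is the natural reading, not a proven one. It does not remove the need for a correction, because the text names an origin other than allocation and uses that word elsewhere for the earlier assessment.

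Three stronger readings are tempting, and the documents do not support them.
- A reader might infer that the clock biases the trial towards one arm. It does not: events before allocation cannot depend on the arm.
- A reader might infer that a real effect on relapse would be missed. The shares above are for a first drink. Three consecutive heavy days should be rarer in an agreed month of abstinence, so dilution should be smaller there. Even for first drink, power at q = 25% is still above half.
- A reader might infer that dating visits from the end of treatment is an error that undermines the primary outcomes. It is a defensible choice for measuring durability after therapy, the fixed date for discontinuers keeps them in follow-up, and the likely shift between arms is a matter of days. TLFB consumption also covers a recent window of 28 days, so a later visit does not simply mean more accumulated relapse. Fixed dates from randomisation could put the post visit before slow completers finish therapy.

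**Conclusion.** The point holds for the time origin of the Cox endpoints. As written, drinking before allocation counts as an event, with attenuation towards 1 and loss of power, and no expected bias towards either arm. Under the assumed inputs, the hazard ratio moves from 0.65 to between about 0.68 and 0.91, and power falls from about 82% to between about 73% and 10%, as washout drinking rises from 10% to 75%. The protocol gives no value for that share; at zero there is no dilution. The conclusion rests on baseline meaning the pre-washout assessment and on randomisation following the washout. It concerns secondary endpoints only, so it is a should-fix. On visit timing, only a modelling refinement is warranted.

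**What to change.** State in the Analyses section that both time-to-event endpoints start at the date of randomisation and count only drinking after it. All randomised participants then enter at time zero, whether or not they drank in the washout. Enter washout drinking (yes/no), taken from the post-washout TLFB that Table 1 already schedules, as a pre-randomisation covariate. That TLFB looks back 28 days, so for washouts longer than this the covariate describes the most recent 28 days.

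As a minor addition, use actual time since randomisation as the time variable in the random effects models, at least as a sensitivity analysis.

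The cost is a few sentences of analysis text and recording the randomisation date. No new assessment is needed and the visit schedule can stay as it is.

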### Hypotheses

1. Participants who receive treatment for alcohol use problems alone will show reductions in alcohol consumption and symptoms of social phobia and improvements on secondary outcomes.

2. Participants who receive the integrated treatment for alcohol use problems and social phobia will show significantly greater improvements in terms of alcohol consumption, social phobia and quality of life compared with those in the alcohol treatment alone. They will maintain a lower rate of alcohol consumption for longer than the alcohol treatment alone group and will have greater improvements on measures of general health and functioning.

3. Participants in the integrated treatment condition will have a lower rate of treatment attrition than participants in the alcohol treatment alone intervention.

4. Higher levels of alcohol dependence will result in relatively poorer outcomes for the integrated treatment.

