All interviews will be audio-taped and a random sample of 25% will be rated by a PhD level Clinical Psychologist with relevant diagnostic experience, to determine diagnostic reliability. Measures used in the study are shown in Table 1 and include: the Anxiety Sensitivity Index [73]; Kushner’s Alcohol Outcome Expectancies Questionnaire [74]; the Timeline Follow-Back (TLFB) method for quantifying alcohol consumption over the previous 28 days [75,76]; the Opiate Treatment Index (OTI) to assess drug (and medication) quantity and frequency during the previous 28 days [69]; the Penn Craving Scale [77]; Self efficacy for abstinence [78]; the University of Rhode Island Change Assessment [79], used to assess motivation; Health Service Utilisation questions [80], used to asses other treatment received in study period.

**Table 1 T1:** Schedule of assessments

**Assessment**	**Telephone contact**	**Pre treatment**	**Post washout**	**Post treatment**	**3 month follow-up**	**6 month follow-up**
*Eligibility*						
Alcohol Use Disorders Identification Test (AUDIT) [64]	+	-	-	-	-	-
Mini Social Phobia Inventory (Mini-SPIN) [65]	+	-	-	-	-	-
Clinical Institute Withdrawal Assessment for Alcohol Revised (CIWA-AR) [70]	+	-	-	-	-	-
Suicide Behaviours Questionnaire-Revised (SBQ-R) [81]	+	-	-	-	-	-
Psychosis Screening Questionnaire [67]	+	-	-	-	-	-
Anxiety Disorders Interview Schedule for DSM-IV (ADIS-IV) [82] incorporating International Personality Disorders Examination Avoidant Personality Disorder questions (IPDE) [72]	-	+	-	-	+	-
*Primary outcome measures*						
Social Phobia Scale and Social Interaction Anxiety Scale (SPS/SIAS) [83]	-	+	+	+	+	+
Time Line Follow Back (TLFB) [76]	-	+	+	+	+	+
Severity of Alcohol Dependence Questionnaire (SADQc) [84]	-	+	+	+	+	+
General Health functioning SF12 [85].	-	+	-	+	+	+
Blood for LFTs, FBC, CDT, Electrolytes	-	+	-	-	+(1)	-
*Secondary outcome measures*						
Sheehan Disability Scale(SDS) [86]	-	+	-	+	+	+
Depression, Anxiety and Stress Scale (DASS-21) [87]	-	+	+	+	+	+
Days out of role from the Brief Disability Questionnaire [88]	-	+	-	+	+	+
Drinker Inventory of Consequences (DRINC) [89]	-	+	-	+	+	+
*Static and varying covariates*						
Family Tree Questionnaire (FTQ)		+				
Anxiety Reduction Subscale of the Alcohol Expectancies Questionnaire [90]	-	+	-	+	+	+
Kushner’s Alcohol Outcome Expectancies Questionnaire [74]	-	+	-	+	+	+
Penn Alcohol Craving Scale(PACS) [77]	-	+	-	+	+	+
Alcohol Abstinence Self Efficacy Scale (AASES) [78]	-	+	-	+	+	+

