### Safety net

Participants who show deterioration in functioning requiring residential or psychiatric treatment will be referred to the appropriate specialist treatment services (anxiety clinics, psychiatric services or alcohol and other drug services). They will remain in the study but their outcome will be designated as relapsed (for anxiety, alcohol or both as appropriate). Either the last point carried forward or multiple imputation will be used to estimate possible scores so as to include these participants in analyses.

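### Last point carried forward is permitted for missing outcome scores; for participants lost during treatment it would enter a pre-treatment drinking or anxiety value as the final outcome

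*Protocol article*

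**What the plan says.** Two places in the protocol article allow last point carried forward (LOCF) as an alternative to multiple imputation. The Analyses section covers people who leave and cannot be found: "Last-point carried forward or multiple imputation will be used to determine the scores of participants who drop-out and are not located at follow-up". The Safety net section covers people who deteriorate and are referred on: "Either the last point carried forward or multiple imputation will be used to estimate possible scores so as to include these participants in analyses". Of the latter it also says: "They will remain in the study but their outcome will be designated as relapsed (for anxiety, alcohol or both as appropriate". Neither place limits LOCF to a sensitivity analysis. The Analyses section also describes the planned random effects model as suited to missing observations.

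On the schedule, the Procedure section states that "all participants will complete a pre-treatment session of motivational interviewing followed by a 1 month “washout” period of abstinence", and places randomisation after that. It then names what is measured: "Symptoms of social anxiety (SPS and SIAS), general anxiety and depression (DASS) will then be reassessed". TLFB and SADQc are not named there. Table 1, however, marks TLFB, SADQc and SPS/SIAS at post washout, with post treatment as the next scheduled assessment. The Assessment section describes "the Timeline Follow-Back (TLFB) method for quantifying alcohol consumption over the previous 28 days". The primary drinking outcome is standard drinks per drinking day from the TLFB.

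Hypothesis 3 reads: "Participants in the integrated treatment condition will have a lower rate of treatment attrition than participants in the alcohol treatment alone intervention". The sample size section allows for 20% attrition during follow-up.

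**The concern.** LOCF assumes that a lost participant's outcome stays at its last recorded value. Here that value is unusually unsuitable. On Table 1, a participant lost during treatment last reported drinking over roughly the washout month, before any randomised treatment. Carrying that record forward would score the person as drinking little or nothing at six months. On the Procedure text, the last drinking record is the pre-treatment one, and the same person would be scored as still drinking at entry level. The plan therefore does not settle what LOCF would impute for a primary outcome.

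For SPS and SIAS both descriptions agree that the last value is post washout, which is still a pre-treatment score. SF12 is not taken post washout, so its carried value would be the baseline one.

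In every case a value from before treatment stands in for an outcome after it, and the filled value is then analysed as if observed, which understates uncertainty. The primary comparison of the arms is at stake.

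**Working it through.** The plan gives no figure for this point, so there is nothing to reproduce. The size below is an illustration.

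**Formula.** Take the difference as integrated minus alcohol alone, so that a positive error counts against the integrated arm. Let d_I and d_A be the proportions filled by LOCF, T_I and T_A the true final means of those lost, and L the carried value.

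Error = d_I(L − T_I) − d_A(L − T_A)

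If those lost have the same true mean T in both arms, this becomes (d_A − d_I)(T − L).

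**Drinking, Table 1 reading.** All inputs are assumed: d_I = 15%, d_A = 25%, T = 5 to 10 drinks per drinking day, L = 0, SD 4 to 6, and all loss before the post-treatment visit.
- T = 5: 0.10 × 5 = 0.5 drinks
- T = 10: 0.10 × 10 = 1.0 drinks
- In SD units: 0.5/6 = 0.08 to 1.0/4 = 0.25, against a planned effect of 0.5
- Gaps of 5 to 15 points: 0.05 × 5 = 0.25 to 0.15 × 10 = 1.5 drinks

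**Drinking, Procedure reading.** If a pre-treatment level is carried and those lost in truth drink less, the sign reverses. With assumed L = 10 and T = 5, the error is 0.10 × (5 − 10) = −0.5. If they have returned to the pre-treatment level, it is 0.

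**Equal loss.** With 20% lost in each arm and no true effect, the error is 0. With assumed final means of 4 and 6, those lost matching their own arm's mean, and L = 0, the error is 0.2(0 − 4) − 0.2(0 − 6) = +0.4. A true difference of −2 shrinks to −1.6. If those lost have the same outcome in both arms, the error is again 0.

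**Social anxiety.** With an assumed carried score of 48 and a true final score of 40 in both arms, the error at 15% v 25% is 0.10 × (40 − 48) = −0.8, which favours the integrated arm. This is the opposite direction from drinking under Table 1.

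**Simulation.** Assumed: 100 per arm, SD 4, alcohol-alone mean 6, loss completely at random before post treatment, carried value near 0 (averaging about 0.8), t-tests, 10,000 runs.

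| Loss, integrated / alone | True difference | LOCF estimate | LOCF rejection | Observed-data rejection |
|---|---|---|---|---|
| 20% / 20% | 0 | 0.00 | 5.0% | 5.2% |
| 15% / 25% | 0 | +0.52 | 14.8% | 5.3% |
| 20% / 20% | −2 | −1.61 | 81.5% | 88.4% |
| 15% / 25% | −2 | −1.18 | 54.7% | 87.8% |

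**Does the alternative remove the problem?** Not if those lost drink more. Assume completers at 4 and lost participants at 8 in both arms, with 15% v 25% lost. The true means are 0.85 × 4 + 0.15 × 8 = 4.6 and 0.75 × 4 + 0.25 × 8 = 5.0, a difference of −0.4. Observed final scores alone give 0, an error of +0.4. LOCF at 0 gives 0.85 × 4 − 0.75 × 4 = +0.4, an error of +0.8. Half of the error remains.

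**The case against.** Several objections limit the point, and most of them stand.

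- **Timing of the choice.** A reader might infer that LOCF or multiple imputation will be picked after seeing the data. The article does not say when the choice is made, and an analysis plan not shown may settle it. Only the permission to use LOCF can be criticised.
- **Hypothesis 3.** A reader might take it as predicting unequal missing data. It concerns leaving treatment. The Analyses section fills scores only for those who also cannot be located. The Procedure section keeps contacting people who stop treatment, and the Participant retention section adds further means of reaching them. A gap in unlocated participants is plausible but is not predicted.
- **Size.** Anyone lost after the post-treatment visit carries that later score, so applying a whole attrition gap to the washout value is upper-range.
- **The carried zero.** Drinks per drinking day is undefined in a fully abstinent window, and is not zero if the participant drank during washout. This weakens the figure, though it is also a reason not to carry the value.
- **Direction.** A reader might conclude that LOCF favours alcohol alone. That holds only for drinking, on the Table 1 reading, with more loss in that arm.
- **Safety net.** A reader might infer that observed scores of people who deteriorate are overwritten. The wording can equally mean filling scores that are missing, alongside a categorical relapse status.

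None of this makes a pre-treatment value a reasonable final outcome.

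**Conclusion.** The concern holds in a limited form and should be fixed. The article authorises LOCF for primary outcome scores in two sections. For a participant lost during treatment and not located, it would enter a pre-treatment value as the final outcome: washout drinking on Table 1, entry-level drinking on the Procedure text, and a pre-treatment anxiety score on either. Bias in the arm comparison arises when loss differs by arm, or when there is a true effect and the outcomes of those lost also differ by arm.

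The 0.5-1.0 drinks (0.08-0.25 SD) is an upper-range illustration for drinking alone. It rests on assumed loss rates, drinking levels, carried value and SD, none of which the document gives. The documents do not support a claim that the trial will be biased by this amount or in a known direction.

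**What to change.** 1. Delete LOCF from the Safety net and Analyses sections.
2. Make the primary analysis the planned random effects model, fitted by likelihood to all observed post-randomisation scores, or multiple imputation under missing at random. Name one as primary.
3. State that actual scores are used whenever participants who stop treatment or deteriorate are assessed.
4. Add a multiple-imputation sensitivity analysis with a worsening shift for those lost. It is needed because the likelihood analysis is also biased if those lost drink more than those observed.
5. Reconcile Table 1 with the Procedure section on whether TLFB and SADQc are taken after washout, and state that the washout value is not used as an outcome.

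The cost is wording in the protocol or analysis plan and one sensitivity analysis. No extra visits are needed, since those who stop treatment are already contacted for assessment.
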